#### Participant Timeline

The 22 participating clinics were randomized in year 1 of the study. These clinics are onboarded in waves throughout the 5-year study period. The time period over which each clinic will experience active study recruitment (with the goal of enrolling 300 patients per clinic) is anticipated to vary from 3 to 12 months, depending on clinic size.

For individual patients in the effectiveness study, the initial screening and recruitment telephone call takes place within 1 week before a patient’s scheduled primary care visit and takes 10 to 15 minutes. Patients are then considered enrolled when they complete their scheduled PCP clinic appointment.

At the intervention clinics, participating patients are asked to arrive up to 1 hour early for their scheduled visit to allow sufficient time for undergoing the 5-Cog battery before meeting their care provider. The 5-minute assessment is completed at the clinic before the appointment.

In both intervention and control groups, patients remain enrolled for 90 days. Study outcomes are ascertained at 90 days (primary and secondary end points), at which point the enrolled patients are considered to have completed participation. This time window was selected because >95% of physician actions for dementia care were completed within this period in our initial trial [33].

Implementation study participants are enrolled when they consent to participate in a survey or an interview, and their enrollment is completed at its conclusion. Figure 2 depicts the study flow.

**Figure 2 figure2:**
[figure not shown]
Study flow. EMR: electronic medical record; PCP: primary care provider; RCT: randomized controlled trial; SES: socioeconomic status.

#### Planned Sample Size

The planned effectiveness study sample size is 6600 enrolled patients, including approximately 300 (4.56%) from each of the 22 participating clinics (Bronx: n=6, 27%; Indiana: n=16, 73%).

For the implementation interviews, we will use snowball sampling to identify the most relevant informants across clinics of different sizes. We anticipate conducting up to 6 implementation interviews per practice for a maximum total sample size of 132 participants or until thematic saturation is reached over the 5-year study period. We will disseminate the quantitative implementation surveys to the clinicians and staff at the intervention clinics.

#### Interventions in the Intervention Arm (5-Cog Battery With Decision Support Tool)

On the day of the patient’s scheduled clinic visit, an RA meets the patient upon their entry into the clinic waiting area in preparation to complete the 5-Cog with them before their PCP visit. The RA escorts the patient through clinic registration. At the same time, the RA communicates with the clinical team to let them know that the patient will undergo the 5-Cog battery before being ready to see their care provider.

The RA administers the 5-Cog (refer to the Introduction section and Figure 1 for more details on the 5-Cog) in a private space within the clinic and then brings the patient back to the waiting area. Next, the RA informs the clinical team that the patient has completed the 5-Cog battery and is ready to be integrated back into the usual clinical workflow. The RA then completes documentation of the battery results in the EMR (and in the study database). The 5-Cog decision support recommendations are harmonized across sites for a positive 5-Cog result, as they are for a negative 5-Cog result (Figure 1).

Montefiore-Einstein and IUH use 2 different EMR systems: Epic (version 100.2412.0.0) and Cerner (version 2024.3), respectively. Unique features within each EMR are used to capture and house the 5-Cog results, create alerts, and present the results and decision support recommendations to the care providers.

At Montefiore-Einstein, the RA creates a “research note.” Here, they input the 5-Cog battery component scores by selecting from a drop-down list for each assessment. They also manually select the appropriate decision support arm (for positive vs negative 5-Cog result) using a quick-text feature. The EMR then responds to the results of the 5-Cog assessments, using structured data elements. Thus, the values that the RA enters for the three 5-Cog battery components trigger a preprogrammed tailored care provider alert, a “best practice advisory” (BPA). If the result of any of the 3 assessments indicates potential cognitive impairment, a “positive 5-Cog” BPA is triggered. If the results do not indicate potential cognitive impairment a “negative 5-Cog” BPA gets triggered. The BPA is “interruptive”; as soon as the care provider accesses the patient’s medical record for the current visit in the EMR, they are shown the alert on their screen. The BPA contains the 5-Cog result with a hyperlink to the research note.

At IUH, the RA inputs the 5-Cog battery result into an EMR-based flowsheet through ad hoc documentation. Specifically, these results are entered into the “Results Review - Clinical Assessment” tab. The EMR is programmed to automatically trigger the appropriate decision support content based on the 5-Cog battery result. As at Montefiore-Einstein, a customized, interruptive alert is displayed to the provider. At IUH, the alert itself contains the 5-Cog result, along with all decision support recommendations.

In both IUH and Montefiore-Einstein EMR flows, care providers must respond to the interruptive alert, acknowledging it in some way. The options for this vary by EMR. At both sites, the alert for patients with a positive 5-Cog result also facilitates linking to an order set. This allows the care provider to efficiently and comprehensively select clinical actions that may be relevant to the patient’s further cognitive care.

Figure 3 depicts a sample of the Montefiore-Einstein and IUH EMR alerts.

**Figure 3 figure3:**
[figure not shown]
Electronic medical record (EMR)–based provider alerts for the intervention sites at the Albert Einstein College of Medicine and Montefiore Medical Center (Montefiore-Einstein; Epic EMR system) and Indiana University Health (IUH; Cerner EMR system). (A) Montefiore-Einstein: positive 5-Cog result. (B) Montefiore-Einstein: negative 5-Cog result. (C) IUH: positive 5-Cog result. (D) IUH: negative 5-Cog result.

At both sites, a paper token (Figure 4) is used as an additional feature to help ensure that care providers review the patients’ 5-Cog results. Patients are handed this token after they complete the 5-Cog battery and are asked to hand it to their care provider at their scheduled visit, generally within 30 minutes after the 5-Cog battery administration.

**Figure 4 figure4:**
[figure not shown]
Token to alert care provider for patient's 5-Cog participation.

#### Interventions in the Control Arm (Enhanced Usual Care)

Patients are screened via telephone using the SCQ, as described in the Recruitment of Clinics and Patients subsection. RAs input results into the EMR. Care providers receive positive SCQ results through noninterruptive alerts. Figure 5 presents images of the alerts at Montefiore-Einstein and at IUH. We are calling this arm “enhanced usual care” because care provider are informed about the presence of a cognitive concern in their patient in this group. In addition, as at the intervention sites, care providers at the enhanced usual care sites receive preparatory education (described in the next subsection). The care providers at the control and intervention sites do not overlap.

**Figure 5 figure5:**
[figure not shown]
Electronic medical record (EMR)–based care provider alerts for the control sites at the (A) Albert Einstein College of Medicine and Montefiore Medical Center (Epic EMR system) and (B) Indiana University Health (Cerner EMR system).

#### Care Provider Education and Preparation in Both Arms

Care providers at both control and intervention sites receive Microsoft PowerPoint presentations on the 5-Cog study. The presentations review the background to the study and then explain the study interventions that will be carried out at the sites (SCQ and new EMR features at both sites; 5-Cog at intervention sites). The presentations last 10 to 15 minutes at the control sites, and 25 to 30 minutes (to allow education about the 5-Cog battery) at the intervention sites. These presentations are provided 2 to 4 weeks before study start at a regularly scheduled clinic staff meeting. In addition to this education, care providers are given brochures that review cognitive impairment detection, diagnosis, treatment, and billing and invited to contact study staff at any time with questions. Finally, they are given tip sheets summarizing the new EMR features. At the intervention sites, care providers are updated on study progress via a monthly email or an informal in-person check-in by a study leader.

Of note, at both intervention and control sites, members of the interprofessional clinic leadership team (administrative and nursing managers) are provided with education on the study procedures and flow so that they can be prepared to assist and appropriately direct any patients who have questions about the study. At the intervention sites, members of the interprofessional clinic leadership team are also engaged in a session to plan clinic-customized logistical workflows to minimize interruptions to the clinic’s operations during the course of the study. These workflows, along with a background to the study, are presented to the full interprofessional clinic staff before study initiation.

#### Interventions for the Implementation Study

From the intervention sites, a subset of patients (after the completion of study procedures and clinic visit) and providers will be invited to complete interviews to assess implementation issues. We will adapt the semistructured CFIR interview question guide. Interviews will be conducted, recorded, and analyzed by study staff trained in qualitative interviewing. We will aim to include patients with both positive and negative 5-Cog results. PCPs and clinical staff at the intervention sites will be asked to complete quantitative surveys containing 3 standardized 4-item measures: the AIM, FIM, and IAM [62]. The implementation outcomes measures are written at a fifth grade reading level; therefore, no specialized training is needed for administration, scoring, or interpretation. Finally, we will retain and later analyze recordings and field notes from our preimplementation stages (initial conversations with clinics and readiness presentations) through the completion of the project. This analysis will assess the barriers and facilitators to primary care sites’ buy-in for study engagement. We will also use summary reports to discern trends in care provider responses to the EMR-based alerts.

#### Interventions for the Cost-Effectiveness Study

Billing and actuarial data will be extracted from the EMR for cost estimation. In parallel fashion to the intervention sites, costs are also collected at the control sites. Standardized cost calculators previously developed by investigators [67,84] will also be used to facilitate microcosting (measuring detailed resource use and unit costs to obtain precise estimates [85]) applicable to the 5-Cog paradigm. We will evaluate the cost of implementing and sustaining the 5-Cog paradigm by accounting for and itemizing specific program characteristics. We will evaluate differences in 5-Cog costs of care on the desired study outcomes compared to enhanced usual care.

#### Effectiveness Study: Primary Outcomes

The primary outcome is a new diagnosis of MCI or dementia within 90 days after study enrollment. Patients who enter the study with a known diagnosis of MCI will only be counted as meeting the primary outcome if they receive a new diagnosis of dementia. We chose diagnosis as the primary outcome for 2 reasons. First, a new diagnosis was a common outcome in our 5-Cog 1.0 study, and we want to validate this finding [33]. Second, this outcome is highly relevant to patients and PCPs: knowing their cognitive diagnosis has been shown to be important to patients and family members [34,86,87]; moreover, diagnostic clarity facilitates appropriate psychoeducation, resource connections, tailored medical treatment, and caregiver activation [88,89].

#### Effectiveness Study: Secondary Outcomes

The secondary outcome is a composite: “improved dementia care” within 90 days after study enrollment. “Improved dementia care” is defined by any of the following actions that are relevant to dementia diagnostic assessment and care: orders for dementia-related laboratory or imaging tests; a new prescription for cognition-enhancing medication or the deprescribing of anticholinergic medication; or referrals to a dementia specialist clinician, a nurse navigator, a social worker, or a community-based organization for related supports. We are including this composite outcome because a new diagnosis without subsequent action is less likely to improve patient outcomes. The aforementioned components are highly relevant to both PCPs and patients [90,91]. The actions described are only counted as an outcome if a cognitive indication (eg, memory loss or MCI) is entered as the indication in the EMR. Tests or referrals without indications entered or performed for any other medical reasons are not counted as outcomes. Prescription of dementia medications will always be counted because these medications inherently indicate cognitive impairment. For anticholinergic deprescribing, actions will be counted via a comparison of EMR-extracted medication lists from the 90 days before and after study enrollment. Charts will be reviewed for clinician notation on whether deprescribing (discontinuation or nonrenewal) was due to a cognitive indication [92]. We will consider the medications listed under “Drugs with strong anticholinergic properties” in the American Geriatrics Society Beers Criteria [93].

All primary and secondary outcomes are collected prospectively from the EMR. Textbox 2 presents a summary of the primary and secondary outcomes.

Study outcomes.
**Primary outcome: new cognitive diagnosis (with associated International Classification of Diseases, Tenth Revision, code [94])**
Vascular dementia with or without modifiers (F01)Dementia in other diseases with or without modifiers (F02)Unspecified dementia with or without modifiers (F03)Mild cognitive impairment or minor neurocognitive disorder (unless patient entered study already having this diagnosis; G31.84)Alzheimer’s disease with late onset (G30.1)Other Alzheimer’s disease (G30.8)Alzheimer’s disease, unspecified (G30.9)Frontotemporal dementia (G31.09)Lewy body dementia (G31.83)Dementia associated with alcoholism (F10.27)Unspecified with psychoactive substance–induced persistent dementia (F19.97)Variant Creutzfeldt-Jakob disease (A81.01)Creutzfeldt-Jakob disease, unspecified (A81.00)Other Creutzfeldt-Jakob disease (A81.09)

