**Composite secondary outcome: “improved dementia care” through relevant actions**
Medications: donepezil, rivastigmine, galantamine, memantine, donepezil-memantine, antiamyloid monoclonal antibody infusions, and any other Food and Drug Administration–approved medications for dementiaDeprescribing anticholinergic medications: discontinuation or nonrenewal of any of the 41 medications in table 7 (“Drugs with strong anticholinergic properties”) of the American Geriatrics Society Beers Criteria [93]Laboratory tests (cognitive indication only): thyroid-stimulating hormone, vitamin B12, glycated hemoglobin, complete blood count, basic metabolic panel, liver tests, HIV antigen and antibody combination, and syphilis immunoglobulin G and immunoglobulin M antibody with reflexImaging tests (cognitive indication only): computerized tomography (head without contrast) and magnetic resonance imaging (brain without contrast)Specialist referrals for cognitive evaluation: geriatrics, neurology, neuropsychology, psychiatry, geriatric psychiatry, and social workCommunity referrals: Alzheimer’s Association or local support organization

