#### Masking

Blinding of patients or PCPs at 5-Cog sites will not be feasible due to the nature of the intervention. However, the outcome is EMR based, and data abstractors will be blinded to allocation. Standardized checklists will be used for outcome measurement to further minimize bias. Statisticians will not be involved in the intervention delivery.

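### The secondary outcome counts tests and referrals only when a cognitive indication is recorded, and the ordering route that may affect recording differs by arm, so part of any difference could be documentation rather than care

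*Protocol article*

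**What the plan says.** In the protocol article, Effectiveness Study: Secondary Outcomes, the composite is met by any listed action within 90 days. An action is "only counted as an outcome if a cognitive indication (eg, memory loss or MCI) is entered as the indication in the EMR", and "Tests or referrals without indications entered or performed for any other medical reasons are not counted as outcomes". Textbox 2 repeats the restriction for imaging and for laboratory work: "Laboratory tests (cognitive indication only): thyroid-stimulating hormone, vitamin B12, glycated hemoglobin, complete blood count, basic metabolic panel, liver tests", followed by HIV and syphilis testing.

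Two components are handled differently. For dementia drugs, "Prescription of dementia medications will always be counted because these medications inherently indicate cognitive impairment". For anticholinergic drugs, medication lists before and after enrollment are compared, and "Charts will be reviewed for clinician notation on whether deprescribing (discontinuation or nonrenewal) was due to a cognitive indication".

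The ordering route differs by arm. In the intervention arm the alert is interruptive and must be acknowledged, and "the alert for patients with a positive 5-Cog result also facilitates linking to an order set". The 5-Cog Paradigm subsection describes this as a menu of laboratory, imaging and referral orders gathered in one place. Trial Design states that control clinics have no decision support tool, and the control-arm section gives them a noninterruptive alert of the positive concern questionnaire.

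On outcome assessment, Masking says "the outcome is EMR based, and data abstractors will be blinded to allocation" and adds standardized checklists. Effectiveness Study: Statistical Plan repeats that assessors are blinded.

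**The concern.** The scoring rule is the same in both arms, but it rests on an act of recording by an unblinded clinician, and the intervention alters the setting in which that act takes place. A B12 level ordered because of memory complaints counts if the reason is entered and scores nothing if the field is blank or general. If ordering from a 5-Cog alert makes a cognitive reason more likely to be entered, the intervention arm gains events without any change in what was ordered.

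This difference arises when the order is placed, before any abstraction, so blinded abstractors cannot remove it. The mixed model cannot remove it either, because the ordering route follows the randomized arm. The article justifies this outcome on the ground that a diagnosis without action is less likely to help patients. An outcome that partly measures labeling would not serve that purpose.

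A narrower point concerns blinding. Deprescribing needs a reader in the chart, and intervention charts contain 5-Cog material. The Bronx research assistant writes a research note with the component scores, and "The BPA contains the 5-Cog result with a hyperlink to the research note". Indiana stores the result in a flowsheet. The article does not say that this material is hidden from abstractors.

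**Working it through.** **Inputs from the article.** 22 clinics of about 300 patients, 1:1, so 3,300 per arm; intraclass correlation (ICC) 0.05; two-sided alpha 0.05; expected secondary outcome 21% vs 7%; stated power above 99%.

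**The plan's own figure.** Design effect = 1 + (300 − 1) × 0.05 = 15.95. Effective size per arm = 3,300 / 15.95 = 206.9. Power for 21% vs 7% is 98.6% (pooled normal approximation) or 97.8% (noncentral t, 22 − 2 = 20 degrees of freedom). This is close to the stated figure, and the concern here is bias, not sample size.

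**Bias illustration.** Let T be the proportion of patients with a true cognitive action, the same in both arms. Let r_I and r_C be the probabilities that such a patient has a recorded, countable action. Observed rates are T × r_I and T × r_C. The values of r are assumptions; the article gives none. With T = 21%:

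| Recording, intervention vs control | Observed rates | Gap (points) | Odds ratio | Chance of a significant result, ICC 0.05 | Same, ICC 0.01 |
|---|---|---|---|---|---|
| 95% vs 80% | 19.9% vs 16.8% | 3.1 | 1.23 | 12% | 35% |
| 95% vs 70% | 19.9% vs 14.7% | 5.2 | 1.45 | 27% | 77% |
| 95% vs 50% | 19.9% vs 10.5% | 9.4 | 2.12 | 73% | >99% |

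The last two columns use the t calculation with 20 degrees of freedom; with no recording gap the chance would be 5%. For the second row: 0.21 × 0.95 = 0.1995 and 0.21 × 0.70 = 0.147; standard error = √[(0.1995 × 0.8005 + 0.147 × 0.853) / 206.9] = 0.037; noncentrality = 0.0525 / 0.037 ≈ 1.4.

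**Not every component depends on the field.** If only half of the actions depend on it, 95% vs 50% becomes 0.21 × (0.5 × 0.95 + 0.5) = 20.5% against 0.21 × (0.5 × 0.50 + 0.5) = 15.8%, and the chance falls from 73% to 22%.

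**Several orders per patient.** One recorded order is enough. If a patient has two orders, each recorded independently with probability 0.70, the patient counts with probability 1 − 0.30² = 0.91. Per-patient gaps can therefore be smaller than per-order gaps.

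**Could recording explain the whole planned effect?** That needs r_C / r_I = 7 / 21 = one third.

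**Effect on a result of the planned size.** If 21% vs 7% were observed with recording of 95% vs 70%, the true rates would be 0.21 / 0.95 = 22.1% and 0.07 / 0.70 = 10.0%, a difference of about 12 points instead of 14.

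**The case against.** The strongest reply is that the causal step is not in the text. A reader might infer that the order set supplies the cognitive indication while control clinicians must type it. The article says only that the alert links to orders. It does not say that an indication is pre-filled, suggested or required, and the figures showing the alerts are not available. This stands: direction and size are inferences.

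The scope is also limited. The order-set link is described only for positive 5-Cog results, clinicians may order outside it, dementia drugs are exempt, and deprescribing uses chart notation. Control clinicians are told of the cognitive concern and receive education and brochures, which may also prompt them to record a reason. All of this narrows the likely gap.

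The rule itself is defensible. Blood counts, metabolic panels, glycated hemoglobin and liver tests are often ordered for other reasons, and without a filter they would count as dementia care. That is a reason to keep the rule as the main definition, not to leave it unchecked.

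A reader might also infer that abstractor blinding must fail. The article does not support that: the sentence on the hyperlink describes the provider's screen, and masking of notes before review may be operational detail left out of a condensed article. What stands is a question about one component.

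Finally, a sensitivity analysis may already be in the unseen SAP. If so, that part of the request is met. The point raised here is a property of the rule that the article itself states.

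**Conclusion.** The concern holds in a limited form. The secondary outcome requires a recorded cognitive indication for tests and referrals, and the ordering environment differs by arm. A recording difference can therefore pass for a care difference, plausibly in favor of the intervention. Under assumed recording of 95% vs 70–80%, identical care would show a gap of about 3 to 5 points (odds ratio 1.23 to 1.45) and, at the plan's ICC, a 12–27% chance of a false significant result. These figures apply the recording rates to the whole composite, so they are on the high side if some components are exempt; they would be more serious at a lower ICC.

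The documents do not support the reading that recording would account for the planned 21% vs 7%, since control recording would have to be one third of intervention recording. Nor do they establish that the bias exists. The primary outcome, a recorded diagnosis, is outside this point. The matter should be addressed because the check is cheap and bears on what the secondary result can be said to mean.

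**What to change.** - Keep the indication-based rule as the main definition. Do not replace it with a rule that counts an order when the visit carries a cognitive diagnosis code. Such diagnoses are what the intervention aims to raise (expected 14% vs 2%), so a routine blood count at a newly coded visit would score mainly in the intervention arm.
- Add a prespecified sensitivity analysis that counts all listed actions within 90 days regardless of indication, by the same query in both arms and reported by component. Include a version limited to less routine items, such as B12, syphilis testing, head imaging, and specialist and community referrals.
- Report, by arm, the proportion of listed orders with any indication and with a cognitive indication. State whether the order set pre-fills or requires one.
- For deprescribing, withhold 5-Cog and concern-questionnaire notes, results and clinic identity from abstractors. Otherwise qualify the blinding statements in Masking and in the Statistical Plan for that component.

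The cost is one broader EMR query, some SAP wording and, if chosen, redaction for the deprescribing review. The drawback is that routine orders add noise and dilute the effect in the sensitivity analysis, so a smaller difference there would not by itself show that the main result is an artifact. The restricted version and the completeness table help with that reading.
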